### Estimation of sample size

This study will adopt the “3 + 3” dose-escalation principle. Seven albumin dose groups will be formed: 0.25, 0.35, 0.40, 0.45, 0.50, 0.55, and 0.60 g/kg. If the primary endpoint is never reached, at least 21 participants need to be included. If one person per dosage group experiences a primary endpoint, 42 participants will be required. A flowchart of the 3 + 3 dose-escalation trial design is shown in Figure 2.

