**Figure 1 fig1:**
[figure not shown]
Flowchart of the first stage of the study.

The inclusion criteria are as follows: (1) age 18–80 years; (2) an anterior circulation large vessel occlusion confirmed using computed tomography (CT), magnetic resonance imaging/magnetic resonance angiography (MRI/MRA), or digital subtraction angiography (DSA); (3) a baseline National Institutes of Health Stroke Scale (NIHSS) score ≥6; (4) an arterial puncture was performed within 24 h of stroke onset (defined as either the time the onset of a neurological abnormality was observed the time when symptoms were first noticed on waking from sleep or the last time the patient was observed to be without stroke symptoms); and (5) the occluded vessel reaches an expanded thrombolysis in cerebral infarction (eTICI) score ≥2b after EVT was confirmed using DSA.

The exclusion criteria are as follows: (1) a history of congestive heart failure or jugular dilatation, third heart sound, resting tachycardia due to heart failure (>100 beats/min), or hepatomegaly and lower limb edema without obvious cause on physical examination at admission; (2) hospitalization for acute myocardial infarction within 3 months; (3) symptoms of acute myocardial infarction or admission electrocardiogram data; (4) second- or third-degree heart block or arrhythmia with hemodynamic instability; (5) acute or chronic renal failure (blood creatinine >2.0 mg/dL); (6) severe anemia (hematocrit <32%); (7) clinically suspected aortic dissection; (8) symptoms or CT evidence of subarachnoid hemorrhage; (9) parenchymal cerebral hemorrhage; (10) pregnancy; (11) allergy to albumin; (12) blood pressure >185/110 mmHg on admission; (13) presence of major lung disease; and (14) presence of other life-threatening diseases.

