### Randomization and blindness

The study will be divided into two stages: a first-stage dose-escalation test and a second-stage safety test conducted with an expanded sample size based on the first stage. In the first stage, three participants will be included in each dose group according to the 3 + 3 dose increment principle (13). Seven dose groups will be set in this stage: 0.25, 0.35, 0.40, 0.45, 0.50, 0.55, and 0.60 g/kg. As this study is the first to use a local arterial infusion of 20% human serum albumin solution in humans, the highest dose will be set at 0.60 g/kg. Phase 2 will enroll at least 15 additional participants who will be administered the highest safe dose level determined from phase 1 (14). The Data Security Monitoring Board will conduct a mid-term review at the end of phase one. The protocol is designed as an open-label treatment; thus, we will employ partial blinding; that is, the clinical evaluator will be blinded, but the operator and participant will not be blinded.

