### Outcomes and assessment procedures

The participants’ demographic information will be recorded on the case sheet, including previous medical history, time of onset and progression of stroke symptoms, location of responsible occlusive vessels, and course of intravascular therapy. Head MRI and MRA will be performed to determine the location of the cerebral infarction and the occluded blood vessels. All participants will be required to complete chest CT, hematology, and NIHSS testing before enrollment. CT scans of the chest and head will be performed within 2–24 h after EVT. Head MRI will be performed 3 days after surgery and the infarct volume will be calculated and compared to baseline. NIHSS scores will be measured at 24 h, 48 h, day 7, or at discharge. The NIHSS, modified Rankin Scale (mRS), and Barthel index will be assessed at day 90. The participants will undergo hematological examinations at baseline and within 24 h after surgery, including routine blood tests, blood biochemistry, coagulation studies, and cardiac function-related indicators.

Primary outcomes (safety assessment): the primary safety consideration of the trial is the risk of symptomatic intracranial hemorrhage (sICH). The secondary safety outcomes are: (1) intracranial hemorrhage; (2) all-cause mortality; (3) adverse events; (4) serious adverse events; and (5) heart failure, pulmonary interstitial edema, and severe allergic reactions to albumin infusion.

Secondary outcomes (efficacy assessment): (1) the proportion of patients with an mRS of 0–2 on day 90 after surgery; (2) the development of a cerebral infarct on day 3 after surgery; and (3) changes in NIHSS scores on day 7 after surgery.

Exploratory terminal: (1) coagulation function and blood count related to platelet and lymphocyte counts; (2) biochemical markers of thrombophilic inflammation, including interleukin-1α, interleukin-1β, interleukin-6, interleukin-10, interleukin-18, transforming growth factor-β, histamine, 5-hydroxytryptophan, TNF-α, coagulation factor XII (FXII), ADAMTS13, vWF, GP VI, GP IIbIIIa, tissue factor and soluble CD40 ligand (CD40L); (3) plasma proteomic profiling of subjects; (4) detection of antithrombotic properties of different doses of albumin by peripheral blood cultures of PBMC or platelet cultures from patients or volunteers.

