Albumin is widely used in clinics and has been found to have neuroprotective effects in animal models of transient and permanent ischemic stroke (29, 30). Through imaging examination of animal models, the neuroprotective effect of albumin was shown to be related to the normalization of signals on MRI diffusion-weighted imaging and the reduction of necrotic changes in the residual injury area (31). In focal ischemic stroke, albumin can reduce the total infarct volume by two-thirds, reduce cerebral edema by three-quarters, improve microvascular perfusion, transport free fatty acids to the infarct area, and extend the treatment window to 4 h (32–34). An important component of albumin’s protective effect is thought to be exerted through intravascular and anti-inflammatory mechanisms, which include hemodilution; beneficial interactions with the vascular endothelium (8); platelet anti-aggregation (9); antagonism of erythrocyte sedimentation (10) and neutrophil-endothelial binding (11); and binding to the local release of nitric oxide, which reduces the concentration of inflammatory mediators, such as free radicals interleukins.

In preclinical and clinical trials of albumin, intravenous infusion of medium and high doses of 25% human serum albumin solution demonstrates a neuroprotective effect in AIS which increases with increasing doses up to 2.05 g/kg (35). However, including additional participants in phase III showed that intravenous administration of a 25% human serum albumin solution at 2.0 g/kg was not associated with the 90-day clinical outcome but was associated with an increased incidence of cerebral hemorrhage and pulmonary edema (36). In a follow-up study, the negative phase III results were found to be caused by the absence of factors controlling vascular recanalization and the high albumin solution dose. Medium- and high-dose hypertonic human albumin solutions carry the risk of causing serious dose-related adverse reactions. In animal model experiments, local arterial infusion of a low-dose (20%) human serum albumin solution showed a good neuroprotective effect (11).

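### As worded, the sample size section makes sICH alone the event that expands a 3 + 3 dose group; infusion-related heart failure, pulmonary edema and severe allergy have no stated role in escalation

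*Protocol article*

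**What the plan says.** All references are to the protocol article.

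- **Estimation of sample size.** There are seven dose groups from 0.25 to 0.60 g/kg under the 3 + 3 principle. At least 21 participants are needed if the primary endpoint never occurs. "If one person per dosage group experiences a primary endpoint, 42 participants will be required". The reader is then referred to Figure 2 for the flowchart.
- **Abstract; Outcomes and assessment procedures.** sICH is the primary outcome and the only event listed as primary. The fifth secondary safety outcome is "heart failure, pulmonary interstitial edema, and severe allergic reactions to albumin infusion".
- **Discussion.** Intravenous albumin at 2.0 g/kg "was associated with an increased incidence of cerebral hemorrhage and pulmonary edema", and medium and high doses of hypertonic albumin "carry the risk of causing serious dose-related adverse reactions".
- **Randomization and blindness.** "The Data Security Monitoring Board will conduct a mid-term review at the end of phase one". On blinding, "the clinical evaluator will be blinded, but the operator and participant will not be blinded".
- **Conclusion.** Finding the maximum safe dose is a main objective.

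**The concern.** In a 3 + 3 design, the event that expands a group from 3 to 6 is the dose-limiting event. It decides which dose is later called safe. The sample size section gives that role to the primary endpoint, so in the visible text only sICH has it.

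The article's own rationale points to a second kind of harm. Of the two harms it reports for high-dose intravenous albumin, only hemorrhage is tied to group size; pulmonary edema is not. The Discussion also says that 20% albumin can expand blood volume by four to five times the infused amount. Taking that at face value for an assumed 70 kg patient at 0.60 g/kg, 42 g of albumin is 210 mL, which implies an expansion of about 840 to 1,050 mL from a 30-minute infusion. Volume overload is therefore a plausible dose-limiting harm, even though the ceiling is well below the intravenous dose (2.0 / 0.60 = 3.3 times lower) and the route differs.

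At stake is the meaning of the dose carried into the second stage. If the visible wording is followed literally, a dose could be labelled the maximum safe dose on sICH alone, despite infusion-related cardiopulmonary or allergic events at that dose.

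**Working it through.** **Step 1: reproduce the stated figures.** 7 groups x 3 = 21, and 7 x (3 + 3) = 42. Both match. They are the headcounts of a 3 + 3 design in which the primary endpoint expands a group.

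**Step 2: chance of passing one dose level.** The usual rule is assumed: pass with 0 events in 3, or with 1 in 3 followed by 0 in the next 3. For event probability p per patient:

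f(p) = (1 - p)^3 + 3p(1 - p)^2 x (1 - p)^3

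Let s be the sICH rate and c the rate of heart failure, pulmonary edema or severe allergy. With sICH as the only trigger, p = s. With a composite trigger and independent events, p = 1 - (1 - s)(1 - c). The article gives neither rate, so all values of s and c are assumptions.

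With s = 5% and sICH only: f(0.05) = 0.8574 + 0.1161 = 0.973, whatever c is.

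| c | composite p | chance of passing, composite | drop from 0.973 |
|---|---|---|---|
| 2% | 0.069 | 0.952 | 2 points |
| 5% | 0.0975 | 0.910 | 6 points |
| 10% | 0.145 | 0.824 | 15 points |
| 20% | 0.240 | 0.622 | 35 points |

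Sensitivity to s, at c = 5%: with s = 2% the chance falls from 0.995 to 0.952 (4 points); with s = 10% it falls from 0.906 to 0.824 (8 points).

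**Step 3: cost of a composite trigger over the whole escalation.** At s = 5%, the chance of clearing all seven levels on sICH alone is 0.973^7 = 0.83. Suppose c rises linearly with dose d from 0 at 0.25 g/kg to c_max at 0.60 g/kg, that is, c = c_max x (d - 0.25) / 0.35. The product of f over the seven levels is then 0.76 for c_max = 2% and 0.65 for c_max = 5%.

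**Step 4: how often such an event would arise in stage 1.** At s = 5%, a group expands (exactly one sICH in its first three patients) with probability 3 x 0.05 x 0.95^2 = 0.135. Expected enrolment if all seven levels are run is 7 x (3 + 3 x 0.135) = 23.8, about 24. The chance of at least one such event in 24 patients, 1 - (1 - c)^24, is 21%, 38% or 71% at c = 1%, 2% or 5%. This is how often the team would face the question, not how often a wrong dose would be chosen: even under a composite rule, one event in three patients only expands the group.

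**The case against.** The strongest reply is that the sentence at issue is a headcount, not an escalation rule. It stands under a sample size heading and hands the design to Figure 2, which is not available here. Figure 2 or the full protocol may define a wider dose-limiting event. This stands, and it limits the point to the wording of that section.

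A reader might infer that the trial has no cardiopulmonary stopping rule, or that a patient with pulmonary edema would have no effect on the next dose. The documents do not support either. The section does not say that only the primary endpoint counts, and it does not say when escalation is held. What can be said is that sICH is the only event given a role, and that no visible sentence gives one to the other harms.

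A reader might also use 42 patients as the exposure, which gives 88% for at least one such event at a 5% rate. That needs exactly one sICH in the first three patients of all seven groups, a chance of 0.135^7, or about 8 in 10 million, at a 5% sICH rate. About 24 patients is the realistic number.

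The existing protections also count. Heart failure, renal failure, albumin allergy and "presence of major lung disease" are exclusions. Vital signs are monitored during infusion, and the ethics committee monitors safety continuously. The pig experiments at 0.50 and 0.60 g/kg showed no cardiopulmonary impairment. The monitoring board reviews the first stage and can act on these events at that point. These measures lower the risk, but none is a stated criterion for moving between dose levels.

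**Conclusion.** The point holds in limited form. As worded, the sample size section ties 3 + 3 group size to sICH alone. Heart failure, pulmonary edema and severe allergic reaction to the infusion have no stated role in escalation, although the article itself names pulmonary edema and dose-related reactions as harms and sets out to find the maximum safe dose. The figures 21 and 42 are correct as 3 + 3 arithmetic.

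The per-level effect is small if these events occur in 5% of patients or fewer: 2 to 6 percentage points at rates of 2% to 5%, with sICH at 5%. It becomes material if a dose proves toxic: 15 points at 10% and 35 points at 20%. Detecting such a dose is the purpose of the escalation. These sizes rest on assumed rates, independent events and the usual 3 + 3 rule. Confidence is medium because Figure 2 has not been seen. If it already uses a wider event, what remains is an inconsistency of wording.

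**What to change.** In Estimation of sample size, and in Figure 2 if it says the same, replace the primary endpoint with a dose-limiting event. Define it as either of the following within a fixed early window:

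- sICH;
- heart failure, symptomatic pulmonary edema or severe allergic reaction at least possibly related to the infusion.

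The window should cover the chest CT already planned at 2 to 24 h and the cardiac indicators already planned within 24 h. The article gives no data on event timing, so the sponsor must fix its length.

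For relatedness, count any such event within the window unless another cause is documented. This avoids a separate adjudicator. The task should not go to the blinded evaluator: every first-stage patient receives albumin, and relatedness to an infusion cannot sensibly be judged without knowing that it was given. Nor does it fit the monitoring board as described, whose stated review comes only at the end of the first stage; up to six between-level judgments would be new work for it.

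Keep sICH as the primary outcome. Do not count all-cause death or unrelated adverse events, since background stroke events could then stop escalation. The range of 21 to 42 is unchanged.

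The cost is protocol wording, a documented cause for any event not counted, and somewhat earlier stopping. On the assumptions in the working, the chance of clearing all seven levels falls from 83% to 76% or 65%. If Figure 2 already defines a wider event, only the sample size text needs aligning.

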**Figure 2 fig2:**
[figure not shown]
3 + 3 dose-escalation trial design.

The second phase is a safety trial with an expanded sample size based on the maximum safe dose determined in the first phase. According to a previous study (14), the safety of the albumin solution arterial infusion can be assessed by including 15 participants in the second phase.

### Statistical analyses

Statistical analysis will be conducted based on the intention-to-treat principle. Continuous variables will be described using the mean or interquartile range for normal distribution. Categorical variables will be expressed as the frequency and percentage. In this study, multiple independent groups will be compared. The Kruskal–Wallis *H* test and the Mann–Whitney *U* test will be used for severely skewed continuous variables, and the t-test will be used for normally distributed continuous variables. The chi-squared test or Fisher’s exact test will be used to compare the difference in binary outcomes between the groups. All statistical tests will be conducted using a two-sided test. A value of *p* < 0.05 will be considered statistically significant. All statistical analyses will be performed using SPSS statistical software, version 26.0.

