**Methods:**

This study is a prospective, therapeutic exploratory, non-randomized, open-label, phase 1 clinical trial testing the use of 20% human serum albumin solution injected via the artery immediately after successful reperfusion in patients with AIS. The study is divided into two stages. In the first stage, a single-dose-finding will explore the maximum safe dose according to the 3 + 3 dose escalation principle;, with the maximum dose being 0.60 g/kg. After recanalizing the occluded blood vessel, human serum albumin solution will be injected into the internal carotid artery region through a guiding catheter for 30 min. The second stage involves an albumin adjuvant therapy cohort (AT) and an endovascular treatment lonely cohort (ET). The AT cohort will encompass at least 15 additional participants to complete safety trials at the maximum safe dose determined in the first stage. The ET cohort will include well-matched patients receiving endovascular therapy alone, derived from a contemporaneous prospective registry, who will be excluded from having cardiopulmonary disorders and from receiving any neuroprotective therapy. The primary outcome of this study will be symptomatic intracranial hemorrhage. Efficacy outcomes will include the proportion of patients with the progression of cerebral infarction volume, a modified Rankin Scale of 0–2 on day 90 after randomization. An exploratory secondary outcome will be the analysis of thromboinflammatory and neuroprotective molecule profiles.

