### Study design

This is a prospective, therapeutic exploratory, non-randomized, open-label, phase 1 clinical trial for testing the use of 20% human serum albumin solution injected via the artery immediately after successful reperfusion in patients with AIS.

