### Interventions

All participants will be recanalized after completing EVT with responsible occlusive vessels of ≥2b, as confirmed by DSA. Participants will receive 20% human serum albumin solution (China Resources Boya Biopharmaceutical Group Co., Ltd.) corresponding to their dosage group and individual body weight. Albumin will be injected into the diseased side of the internal carotid artery with an infusion time of 30 min. The patient’s blood pressure, heart rate, respiratory rhythm, and oxygen saturation will be monitored throughout the transfusion process. The operative method for the participants will be determined independently by the neuro-interventional physician, who will choose either mechanical thrombectomy or stent insertion according to the intraoperative conditions. All participants will be treated in accordance with the latest Chinese clinical Guidelines for AIS.

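### Intention-to-treat is the only analysis principle stated for a non-randomised dose-finding safety trial; read literally, it analyses safety by planned rather than received albumin

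*Protocol article*

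**What the plan says.** All places are in the Protocol article.

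- *Statistical analyses* opens with the only analysis principle in the document: "Statistical analysis will be conducted based on the intention-to-treat principle". The rest of that section covers descriptive summaries, between-group tests and the significance level.
- *Study design*: "This is a prospective, therapeutic exploratory, non-randomized, open-label, phase 1 clinical trial".
- *Outcomes and assessment procedures* makes sICH the primary outcome. Other haemorrhage, death, adverse events, heart failure, pulmonary oedema and allergic reactions are secondary safety outcomes.
- *Participants and screening* places enrolment after recanalisation has been confirmed. Exposure comes after that, under *Interventions*: "Albumin will be injected into the diseased side of the internal carotid artery with an infusion time of 30 min".
- The escalation scheme is described elsewhere. *Randomization and blindness* says "three participants will be included in each dose group". *Estimation of sample size* says "Seven albumin dose groups will be formed", then "If the primary endpoint is never reached, at least 21 participants need to be included" and "If one person per dosage group experiences a primary endpoint, 42 participants will be required". The flowchart in Figure 2 is not available in the text reviewed.
- The Abstract times the mRS outcome "on day 90 after randomization". The Outcomes section counts the same 90 days from surgery.

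**The concern.** Intention-to-treat keeps patients in the arm to which they were randomised, so that comparability survives non-adherence. Nobody is randomised here, so it has nothing of that kind to preserve. What it still does is attach each patient to a planned dose.

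For a question about dose-related harm, that is the wrong attachment. Enrolment comes before the infusion, so a patient can belong to a dose group and receive none or part of that dose. Such a patient stays in the denominator at the nominal dose. If albumin at that dose raises the sICH risk, the group's rate is diluted toward the rate seen after endovascular treatment alone. The groups are small (three or six patients per level, at least 15 in stage 2), so one or two such patients matter. The trial exists to find a maximum safe dose and then to describe safety at it, so the error would usually lean toward reassurance.

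The article does not leave the analysis set open for a later document to define. It states one, and a later safety set based on exposure would contradict it.

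**Working it through.** **1. The plan's own figures.** Seven levels × 3 patients = 21, and seven levels × 6 patients = 42. Both stated totals reproduce, and this point does not affect them. They fit the textbook rule: pass a level on 0/3, or on 1/3 followed by 0/3 in a second cohort. That rule is an assumption below, because Figure 2 is not shown.

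**2. Direction of the dilution.** Let p be the sICH risk with the full dose, b the background risk without albumin, and q the fraction of the group not infused. The expected rate at the planned dose is

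(1 − q)p + qb.

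This is below p if b < p, equal to p if b = p, and above p if b > p. The article gives none of the three values, so all are assumed here. Example for stage 2: 13 of 15 infused, p = 20%, b = 5% gives (13 × 0.20 + 2 × 0.05)/15 = 2.7/15 = 18%, against a true 20%.

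**3. Escalation, only if the principle were carried over to it.** With everyone infused,

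P(pass) = (1 − p)³ + 3p(1 − p)² × (1 − p)³.

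At p = 0.20 this is 0.512 + 0.384 × 0.512 = 0.709.

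With one of the first three uninfused but counted, and the second cohort fully infused,

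P(pass) = (1 − p)²(1 − b) + [2p(1 − p)(1 − b) + (1 − p)²b] × (1 − p)³.

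At p = 0.20:
- b = 0: 0.640 + 0.320 × 0.512 = 0.804
- b = 0.08: 0.5888 + 0.3456 × 0.512 = 0.766

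If instead each patient has a 10% chance of not being infused and b = 0.05, the risk per counted patient is 0.9 × 0.20 + 0.1 × 0.05 = 0.185. The first formula then gives 0.741.

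| Full-dose risk p | All infused | One of first three uninfused, b = 0 / 5% / 8% | 10% non-infusion per patient, b = 5% |
|---|---|---|---|
| 5% | 0.973 | 0.984 / 0.973 / 0.967 | 0.973 |
| 10% | 0.906 | 0.941 / 0.924 / 0.913 | 0.914 |
| 20% | 0.709 | 0.804 / 0.780 / 0.766 | 0.741 |
| 33% | 0.434 | 0.582 / 0.560 / 0.546 | 0.490 |

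The 5% row shows the limits of the argument: no shift when background equals full-dose risk, and a small reversal when background is higher.

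**4. Stage 2 precision.** With no events in n patients, the one-sided 95% upper bound is 1 − 0.05^(1/n).
- n = 15: 18.1%
- n = 13: 20.6%

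A report of 0/15 with two patients uninfused would therefore claim a bound 2.5 percentage points tighter than the exposed patients support.

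**The case against.** A reader might infer that intention-to-treat governs the 3 + 3 decision, and that an uninfused or part-infused patient is entered there as a full-dose patient without toxicity. The document supports neither step.

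- The sentence concerns statistical analysis, in a section about summaries and tests. The escalation rule sits elsewhere and uses none of those tests. Its effect on escalation is a possible reading, not a stated rule.
- Intention-to-treat fixes the group, not the outcome. An sICH after a partial infusion, or after none, remains an event, including one that caused the infusion to be stopped. What can happen is dilution toward background, not loss of the event.

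The size is also open to challenge. The 0.80 figure supposes that one patient in three is certainly uninfused and has no sICH risk, although that patient has just had a large-vessel stroke and endovascular treatment. The drug is a single 30-minute infusion given straight after reperfusion, so missed or broken-off infusions are plausibly uncommon. The 10% scenario shows a much smaller shift. Finally, rules on evaluability and replacement may stand in the full protocol, the SAP or Figure 2, and their absence from an article is no fault.

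All of this stands, and it limits the harm that can be claimed. It does not make the stated principle suitable: an exposure-based safety outcome in a non-randomised trial is still assigned an analysis by intention. The Abstract's mention of randomisation is a wording slip that the Outcomes section already resolves, and it adds no weight to the dilution argument.

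**Conclusion.** The concern holds in a limited form. The article states intention-to-treat as its sole principle for a non-randomised phase 1 trial whose primary outcome is sICH. Taken literally, this dilutes the dose-specific and stage 2 sICH rates toward background whenever full-dose risk exceeds background and some enrolled patients are not fully infused.

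The consequence for reported rates follows from the text. The consequence for escalation is an illustration only. At 20% risk it ranges from 0.71 to 0.74 under occasional non-infusion, and from 0.71 to 0.77–0.80 if one of the first three patients is uninfused. These figures rest on an assumed textbook 3 + 3 rule, background risk and under-infusion frequency. In the stage 2 example the bound moves from 18.1% to 20.6%. This is a moderate flaw in a stated rule. It is not evidence that escalation will be unsafe.

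**What to change.** - For sICH and all other safety outcomes, replace intention-to-treat with a safety set of all patients who received any albumin, analysed by the dose actually received.
- State that patients who received no albumin do not count as evidence that a dose is safe.
- Keep patients whose infusion was stopped early in the safety data and report the reason. Restricting the data to completed infusions would discard those stopped for intolerance other than sICH. Show the planned level beside the received dose, so that an event that ended an infusion is not credited only to a smaller dose.
- Reconcile the Abstract's day-90 time origin with the one in the Outcomes section, since there is no randomisation date.

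The cost is a few sentences of analysis-set wording, slightly smaller safety denominators, and possibly an occasional additional patient in stage 1.

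### The non-randomised comparison of albumin patients (AT) with registry controls (ET) has only unadjusted tests for independent groups behind it, so residual baseline differences may be read as albumin effects

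*Protocol article*

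**What the plan says.** The Study design section describes the trial as follows: "This is a prospective, therapeutic exploratory, non-randomized, open-label, phase 1 clinical trial".

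The control cohort is described only in the Methods paragraph of the abstract: "The ET cohort will include well-matched patients receiving endovascular therapy alone, derived from a contemporaneous prospective registry". The one further restriction stated for these controls is "who will be excluded from having cardiopulmonary disorders and from receiving any neuroprotective therapy". The body text on stage 2 (Randomization and blindness; Estimation of sample size) mentions only the additional albumin patients, at least 15 of them.

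The Statistical analyses section is the only analysis text. It says "In this study, multiple independent groups will be compared", assigns rank tests or the t-test to continuous variables, and adds: "The chi-squared test or Fisher’s exact test will be used to compare the difference in binary outcomes between the groups". All tests are two-sided at 0.05. No covariate, propensity method or matched analysis is named.

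The efficacy outcomes (Outcomes and assessment procedures) include mRS 0–2 at day 90 and "changes in NIHSS scores on day 7 after surgery". The Limitations section accepts that the lack of full random allocation may cause selection bias.

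**The concern.** ET is the only cohort without albumin, so any comparative efficacy statement has to come from AT versus ET. In a non-randomised comparison, an unadjusted test measures the treatment effect plus whatever prognostic difference remains between the cohorts.

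There is a visible route for such a difference. AT patients must satisfy "the occluded vessel reaches an expanded thrombolysis in cerebral infarction (eTICI) score ≥2b after EVT was confirmed using DSA" and must pass exclusions for renal failure, severe anemia, high admission blood pressure and other life-threatening disease. The article does not say that ET patients meet the same criteria. If the matching does not cover these features, AT may be the better-prognosis group, which would favour albumin.

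The article says its results will supply data parameters for later trials, so a confounded difference could be carried into the next trial's effect size.

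**Working it through.** **The plan's own figures.** The only sample sizes derived in the plan are for stage 1: 7 dose groups × 3 = 21 with no events, and 7 × 6 = 42 with one event per group. Both reproduce. There is no stated size, power or outcome rate for AT versus ET, so what follows is an illustration under assumptions.

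**Inputs from the article.** AT has at least 15 patients; tests are two-sided at 0.05; the binary outcome is mRS 0–2 at day 90.

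**Assumptions.** No true albumin effect; ET rate of mRS 0–2 of 45%; one standardised prognostic factor with log-odds slope g = 0.7 or 1.0 per SD (odds ratio 2.01 or 2.72); ET size of 15, 45 or 60; residual imbalance of d SD in favour of AT.

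**Binary outcome.** Model: logit P = c + g(x + d), with x standard normal and c chosen so that d = 0 gives 45%. Averaging over x gives the AT rate:

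| d (SD) | AT rate | Spurious difference | Spurious odds ratio |
|---|---|---|---|
| 0.25 | 48.9–50.2% | 3.9–5.2 points | 1.17–1.23 |
| 0.5 | 52.9–55.3% | 7.9–10.3 points | 1.37–1.51 |
| 0.75 | 56.8–60.3% | 11.8–15.3 points | 1.60–1.86 |

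Exact enumeration of the rejection rate at d = 0.5, when there is no treatment effect:

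| AT v ET | Chi-squared, d = 0 | Chi-squared, d = 0.5 | Fisher, d = 0.5 |
|---|---|---|---|
| 15 v 15 | 4.6% | 6.6–8.0% | 2.7–3.4% |
| 15 v 45 | 5.0% | 8.1–10.3% | 5.7–7.5% |
| 15 v 60 | 5.5% | 9.4–12.1% | 7.4–9.7% |

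Fisher's test at 15 v 15 stays below 5% because it is conservative; the estimated difference is just as biased.

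**Continuous outcome.** If the outcome has correlation ρ with the factor, the bias is ρd in outcome SDs. With s = √(1/n₁ + 1/n₂), the rejection rate is Φ(ρd/s − 1.96) + Φ(−ρd/s − 1.96). At d = 0.5 and ρ = 0.3 to 0.7 the bias is 0.15 to 0.35 SD. The rejection rate is 7.0 to 16.0% at 15 v 15 (s = 0.365) and 7.9 to 21.7% at 15 v 45 (s = 0.298).

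**Scale.** At 15 v 15 and rates near 50%, the unadjusted SE of a difference in proportions is √(2 × 0.25/15) = 0.183, or 18 points. A bias of 8 to 10 points is about half of that, or 1.2 to 1.5 patients in 15.

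**Precision for NIHSS.** With equal variances and baseline/day-7 correlation r, ANCOVA has (1 − r²)/(2(1 − r)) = (1 + r)/2 of the variance of an unadjusted change score: 0.65, 0.75 and 0.85 at r = 0.3, 0.5 and 0.7. This concerns efficiency, not validity.

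**Symptomatic hemorrhage.** With 0 events in 15, the exact two-sided 95% upper limit is 1 − 0.025^(1/15) = 21.8%. At this size an interval tells the reader more than a between-group p-value.

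**The case against.** The strongest reply is that the Statistical analyses section never names AT, ET, the registry or the matching. Its reference to several independent groups, with Kruskal–Wallis, fits the dose groups, which are indeed independent. This stands in part. A reader might infer that the plan expressly ties these tests to AT versus ET, or that the word independent is an error; the text supports neither. It is nevertheless the only analysis text, and its sentence on binary outcomes is general.

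Second, a condensed article may leave matching and modelling to fuller documents. That is fair for the matching variables and ratio, which are not criticised here. But the article does name a family of tests, and none of them can adjust.

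Third, a reader might infer that a large baseline gap, such as 3 NIHSS points, is to be expected. With an assumed SD of 6, the SE of 6√(2/15) = 2.19 points describes chance differences between unmatched samples; matching on NIHSS would shrink it.

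Fourth, a reader might infer that the standard errors are invalid because matching is ignored. That presumes individually matched sets, which the article does not state. With positively correlated pairs, ignoring the pairing normally makes the SE too large, which is conservative.

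Fifth, ANCOVA is not automatically less biased than a change score in non-randomised groups. That is true, and it is a reason to report both.

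Finally, the trial is exploratory, its primary outcome is symptomatic hemorrhage, and dose escalation does not depend on this comparison. This limits the severity but leaves the efficacy comparison without an adjusted estimate.

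**Conclusion.** The point holds at should-fix level. A non-randomised comparison with registry controls is planned, the only stated analyses are unadjusted tests for independent groups, and the conceded selection bias has no analytic answer. Residual baseline differences may be read as albumin effects. The documents do not support saying that they will be, because adequate matching would remove part of them and no passage commits to a causal reading.

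The size is illustrative: about 8 to 10 points on mRS 0–2 for a 0.5 SD residual imbalance, resting on the assumed 45% rate, prognostic strength and absence of a true effect. The main harm is a biased estimate. False-positive inflation is modest at 15 v 15 and grows if ET is larger. The safety aim and dose finding are little affected.

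**What to change.** For AT versus ET, state in the analysis section:

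- **Main efficacy analysis:** a baseline-adjusted estimate with a 95% CI. Day-7 NIHSS by ANCOVA on baseline NIHSS and age; day-90 mRS 0–2 by Firth logistic regression on baseline NIHSS and age. Use no more than two covariates at about 15 per group.
- **Matching:** if controls are individually matched, allow for the sets, for example with set-clustered standard errors.
- **Sensitivity:** keep the listed unadjusted tests in this role.
- **Wording:** confine the reference to independent groups to the dose-group comparisons, and label AT versus ET exploratory.
- **Symptomatic hemorrhage:** report descriptively with exact confidence intervals.

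The cost is some rewording and a little analysis work, with no new patients or visits. Baseline NIHSS and age are entry criteria for trial participants. That the registry holds both is an assumption to confirm. The limitation is that so small a sample supports few covariates, so confounding by other factors will remain possible and should be acknowledged when the result is reported.
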